### Cryotherapy

Mode of cryotherapy will be standardised across groups (melting iced water [0°C] in a standard sized pack). Clear plastic commercial ice cube bags (17 cm × 28 cm) will be completely filled with water and frozen. Before application, ice packs will be held under hot running water for 30 seconds and wrapped in a single layer of towelling (moistened until just dripping wet). The packs will then be placed over the lateral aspect of the ankle joint, covering an area from the Achilles tendon to the anterior tibialis muscle, with the approximate center of the pack overlying the anterior talofibular ligament (ATFL). Compression will be applied over the pack using 8 cm cohesive bandaging with approximately 5–6 cm of stretch (Figure 3). Timing of the cryotherapy protocol will begin as soon as the compression bandage is in place. A standard verbal explanation and step by step written instructions of the correct procedure for ice pack preparation and application will be given. All necessary equipment will be provided.

**Figure 3 F3:**
[figure not shown]
Method of ice pack application.

### Exercise

Subjects in group II will be provided with verbal and written instructions, and a DVD demonstrating each of the additional exercises. The exercise component (Table 1) has been adapted from a standard written protocol [36] and is designed to take approximatly 10 minutes to complete.

**Table 1 T1:** Therapeutic exercises for treatment group II

**Exercise**	**Repetitions**	**Time (Sec)**
Circumduction (clockwise/anticlockwise)	20	60
Active pf/df	20	60
Static ev/in/pf/df (with 10 second hold)	5 of each	300
Heel slides (with lower limb triple extension)	30	120
Static calf stretch (with 30 second hold)	3	60

pf = plantar flexion. df = dorsi flexion. ev = eversion. in = inversion.

### Follow-up procedure & blinding

At week 1 post injury, function, pain and swelling (outcome measures i, ii, and iii) will be re-assessed by the same researcher who shall remain blinded to group allocation throughout the trial. The activity monitor will also be removed for data collection at this stage (outcome measure iv). Subjects will hand their treatment diaries to the Research Physiotherapist who will re-assess the injured ankle. Follow-up ultrasound images (outcome measure v) shall be taken in those subjects recruited through the University Sports Injury Clinic. After week 1, individual treatment will be progressed in both groups according to clinical need, but will follow a standarised protocol consisting of early, intermediate and advanced stage muscle strengthening, proprioceptive and functional exercises. Subsequent follow-ups shall take place at weeks 2, 3 and 4. Researcher blinding is described in Table 2.

**Table 2 T2:** Blinding of each researcher during trial.

Researcher	Role	Blinding status
RP1	Recruitment, assessment, randomisation and treatment	Unblinded
BA	All baseline and follow-up recording of function, pain, swelling and activity levels (outcome measures i, ii, iii, iv)	Blinded to group allocation
RP2	US images (outcome measure v)	Blinded to group allocation
IR	Interpretation of US images (outcome measure v)	Blinded to group allocation

RP = Research Physiotherapist. BA = Blinded Assessor. US = Ultrasound. IR = Independent Researcher.

### Additional follow up study

In a sub-section to the main trial, longer term function and ankle muscle strength will be examined in a sample of study subjects at 3 months post-injury. While chronic instability and recurrent injuries are a frequent complication following an initial sprain, the precise reasons why such injuries tend to reoccur are unclear at present, and as a consequence rehabilitation may be problematic. It has been suggested that specific evertor muscle strength deficits might be a significant factor in the pathogenesis of CAI [37,38]. However, other evidence does not support this contention [39,40]. Previous research has examined conventional eccentric to concentric ratios of individual muscle groups, or concentric evertor to invertor ratios [39-42]. Since dynamic joint stabilization is achieved by co-contraction of the muscles surrounding the joint, it might be more appropriate to divide the eccentric moment of the antagonist by the concentric moment of the agonist [43]. Examination of such dynamic, reciprocal muscle-group ratios represents an alternative approach to the assessment of muscle strength deficits and imbalance following ankle sprain [44]. Here, muscle strength will be assessed using a KinCom 500H isokinetic dynamometer (Chattecx Corp., Hixson, TN). Isokinetic dynamometers provide an accommodating resistance throughout full range of motion, and have been shown to provide a safe and reliable measure of ankle strength [45]. Eccentric and concentric peak torque values for eversion, inversion, plantar flexion and dorsi flexion will be recorded at a velocity of 60° sec^-1^. Raw data will be normalised for body weight before dynamic ratios are calculated and compared to the un-injured (control) ankle. For example, the eccentric eversion to concentric inversion (eE/cI) ratio for a subject with a body weight (BW) of 88 kg is calculated in the following way: If eE = 81 Newton metres (N.m) (eE/BW = 0.92 N.m/kg) and cI = 92 N.m (cI/BW = 1.15 N.m/Kg), the eE/cI ratio would therefore be 0.92/1.15 = 0.80.

### Sample size

Using data from a previous published study [32] an appropriate sample size for the main trial has been determined using the formula shown in Figure 4[46]. Based on a clinically meaningful difference for the primary outcome measure of 9 points, and allowing for a 10% attrition rate, a minimum number of 60 subjects will be required for each treatment group (assuming 80% power and a 0.05 alpha value).

**Figure 4 F4:**
[figure not shown]
Formula used for sample size calculations.

Using the same formula, a sample size calculation has also been carried out to determine the number of subjects required in the 3 month follow up study. This calculation is based on published data [47] and a clinically meaningful difference between ankle muscle strength ratios of approximately 30%. 30 subjects will be required with the un-injured ankle acting as the control.

### Statistical analysis

Analysis will be on an intention to treat basis. Data will be analysed using SPSS (Windows Version 14.0). Assuming data is from a normal distribution, descriptive statistics will be performed to produce standard deviations (SD), standard errors of the mean (SEM) and 95% confidence intervals (CI). For all outcome measures, a within subject repeated measures analysis of covariance (ANCOVA) will be calculated to determine significant changes over time between groups. Treatment group (two levels: standard and cryokinetic ice application) will be the between subjects factor. Time (four levels: week 1, 2, 3 & 4) will be the within subject factor, with baseline values (week 0) used as the covariate. Where Mauchley's test reveals the assumption of sphericity had been violated the Greenhouse-Geisser epsilon procedure will be carried out to adjust the degrees of freedom accordingly. For all analysis Tukey's test will be used to make *post hoc *adjustments for multiple comparisons. If any significant interactions are detected between treatment group and time point, a univariate analysis of covariance will be used to indicate the time point at which significant differences are found. If required, analyses will be undertaken using the expectation maximisation algorithm method to impute missing values [48]. A number needed to treat (NNT) analysis will also be carried out. For the 3 month follow-up study, a 2 × 2 ANOVA will be calculated to determine if any significant differences exist between isokinetic ratios of subjects injured and un-injured (control) ankles. The level of significance for all tests will be set at p < 0.05.

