### Inclusion/exclusion criteria

Patients with an acute grade I or grade II sprain will be included in the trial on the basis of a standard physical examination of the acutely injured ankle. As part of this assessment, the following demographic information will be recorded: date of birth, height, mass, gender, limb dominance and occupation. Activity level prior to injury will also be recorded and used to group patients according to whether they are from an athletic (defined as participating in high-intensity exercise for more than 90 minutes at least 3 times per week) or non-athletic population.

Patients will be excluded if any of the following criteria are present: Complete (Grade III) ankle ligament rupture (mechanical instability diagnosed by a positive anterior drawer or inversion stress test); Bony ankle injury (indicated by Ottawa ankle rules [31] or plain x-ray); Multiple injuries (e.g. other joint injury or fracture); Ankle sprain more than 1 week since injury; Any contraindication to cryotherapy including cryoglobinaemia, peripheral vascular disease or Raynaud's syndrome. Subjects will also be excluded if they are non-English speaking, have any condition which will affect understanding and communication, are under the influence of drugs/alcohol, or if there is no sufficient address given for follow-up.

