### Treatment allocation

A statistician who will have no contact with the day to day running of the trial shall carry out all aspects of preparation for group randomisation. 184 randomisation envelopes will be produced in the following manner: 92 cards will be printed with **Group I (standard ice application)**. 92 cards will be printed with **Group II (cryokinetic ice application)**. Each card will be placed inside an opaque envelope with carbon paper on top. A randomisation sequence will then be generated using computer software. Stratified randomisation will be employed according to whether subjects are from an athletic (A) or non-athletic population (N). Separate block randomisation sequences will be produced for each stratum using an allocation ratio of 1:1 and a block size of 4 to ensure comparison groups are of approximate size. Envelopes for each stratum will be labeled sequentially (1A-92A & 1N-92N). Envelopes will then be sealed and signed across the seal. Following baseline assessment, these instructions, in sequentially numbered opaque sealed envelopes, will be used to assign sequentially enrolled subjects to one of the two treatment groups. Subjects shall therefore be randomised to treatment groups under strictly double-blind conditions. Before opening the envelope, the Research Physiotherapist will write the subjects unique identification number (stratification number & date of birth) on the outside of the envelope, transferring this information to the instruction card. At the end of the trial this will allow the Principle Investigator to check each card against the original randomisation lists and verify that all subjects received the treatment to which they were assigned.

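### Athletic status stratifies the randomisation but is left out of the ANCOVA, which gives up some precision if it predicts outcome beyond baseline

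*Protocol article*

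**What the plan says.** Under Inclusion/exclusion criteria, patients are grouped before randomisation as athletic, meaning "participating in high-intensity exercise for more than 90 minutes at least 3 times per week", or non-athletic. Treatment allocation makes this grouping the only stratifier: "Separate block randomisation sequences will be produced for each stratum using an allocation ratio of 1:1 and a block size of 4".

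The Statistical analysis section then sets out one model for every outcome, term by term: "Treatment group (two levels: standard and cryokinetic ice application) will be the between subjects factor". It continues: "Time (four levels: week 1, 2, 3 & 4) will be the within subject factor, with baseline values (week 0) used as the covariate". A significant treatment-by-time interaction leads to univariate ANCOVAs that locate the week of the difference. Athletic status appears in none of these models, and no other section brings it into the analysis.

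**The concern.** Blocking within strata balances athletic status between the arms, so differences between athletes and non-athletes contribute almost nothing to the true sampling variability of the treatment difference. A model without the stratum still counts those differences as residual variance. Its standard error then overstates the true one, confidence intervals are too wide and the test rejects less often than its nominal level.

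This happens only to the extent that athletic status predicts the outcome after adjustment for baseline. That is plausible: baseline function is measured on an acutely sprained ankle, whereas the stratum describes activity before the injury, so baseline need not absorb it. At stake is precision that the design has already secured, not the validity of the result. Because the model terms are written out explicitly, this is a mismatch between design and stated model, not detail left to a fuller plan.

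**Working it through.** **Inputs from the protocol.** Sample size section: "Based on a clinically meaningful difference for the primary outcome measure of 9 points, and allowing for a 10% attrition rate", with 80% power and alpha 0.05, "a minimum number of 60 subjects will be required for each treatment group". Two-sided testing is assumed. The SD of the Lower Extremity Functional Scale (LEFS) is not given.

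**Step 1: the plan's own figure.** Without the SD, 60 per group can be checked only for consistency. Evaluable patients per group: 60 × 0.9 = 54. Solving n = 2·SD²·(1.960 + 0.842)²/9² for SD gives SD = 9·√(54/2)/2.802 = 16.69. An SD of 16.5 gives 53, inflated to 59; an SD of 16.7 gives 55, inflated to 62. The stated size therefore corresponds to an SD of about 16.7.

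**Step 2: effect of leaving out the stratum.** Let R² be the share of the baseline-adjusted variance explained by athletic status (assumed, varied from 0 to 0.30).

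- Model SE without the stratum: 16.69·√(2/54) = 3.21.
- True SE under stratified blocking: 3.21·√(1 − R²).
- Ratio of model SE to true SE: 1/√(1 − R²).
- Actual alpha: 2·[1 − Φ(1.960/√(1 − R²))].
- Power without the stratum: Φ(9/true SE − 1.960/√(1 − R²)).
- Power with the stratum: Φ(9/true SE − 1.960).

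| Assumed R² | Model SE too large by | Actual alpha | Power without stratum | Power with stratum |
|---|---|---|---|---|
| 0 | 0% | 0.050 | 80.0% | 80.0% |
| 0.05 | 2.6% | 0.044 | 80.6% | 82.0% |
| 0.10 | 5.4% | 0.039 | 81.3% | 84.0% |
| 0.20 | 11.8% | 0.028 | 82.7% | 88.0% |
| 0.30 | 19.5% | 0.019 | 84.3% | 91.8% |

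The loss is 82.0 − 80.6 = 1.4 points at R² = 0.05 and 84.0 − 81.3 = 2.7 points at R² = 0.10.

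**Step 3: simulation.** 8,000 trials per setting, 108 patients in two equal strata, blocks of 4, ANCOVA on the follow-up mean. At R² = 0.10 the mean SE is 3.22 without and 3.06 with the stratum, type I error 0.040 against 0.051, and power 80.5% against 83.3%. At R² = 0.20 the SEs are 3.23 and 2.88, type I error 0.031 against 0.052, and power 81.0% against 87.2%. At R² = 0 both models give the same power, 78.9%; the shortfall from 80% there is therefore not due to the omission.

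**Step 4: how much baseline already absorbs.** Assume 44 of 108 patients are athletic, a within-stratum baseline correlation of 0.5 and unit SD. The residual variance with the stratum in the model is 1 − 0.5² = 0.75. A gap g between strata adds g²·(44/108)·(64/108) = 0.2414·g² to a variance.

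- Gap at follow-up only. For g = 0.8 the residual variance is 0.75 + 0.1545 = 0.9045, and the SE ratio is √(0.9045/0.75) = 1.10. For g = 0.5 the ratio is √(0.8103/0.75) = 1.04.
- Same gap at baseline and follow-up. For g = 0.8 the residual variance is 1.1545 − 0.6545²/1.1545 = 0.7835, and the ratio is 1.02. For g = 0.5 it is 0.7642, and the ratio is 1.01.

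The excess in the SE thus falls from 4–10% to 1–2% when the gap is already visible at baseline.

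**Step 5: which tests are affected.** A stratum gap that stays constant from week 1 to week 4 cancels from every within-subject contrast, so it does not enter the error term of the treatment-by-time interaction. The excess SE applies to the between-subjects treatment effect and to the univariate ANCOVA at each week.

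**The case against.** The strongest reply is that the loss is conditional and may be trivial. The protocol gives no stratum effect, no athletic proportion and no baseline correlation. Baseline is already in the model and may take up most of any stratum difference. The interaction test that opens the way to the week-specific comparisons is unaffected by a constant gap. The estimate is unbiased, alpha does not exceed 5%, and nothing in the protocol contradicts itself. All of this stands, and it limits the point to a modest gain in efficiency.

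A reader might infer more, in three ways that the document does not support.

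- **That the trial is left short of its planned power.** If the planning SD includes variation between athletes and non-athletes, the model as written keeps about 80% and the adjusted model exceeds it. Even with the whole gap absent at baseline, under the Step 4 assumptions and a 9-point effect (9/16.7 = 0.54 SD), simulated power is 88% against 89% for a 0.5 SD gap and 85% against 89% for 0.8 SD. Figures well below 80% require an effect smaller than the 9 points planned for.
- **That athletic status was chosen because it predicts function.** The protocol gives no reason for the choice.
- **That the whole repeated measures analysis is affected.** Step 5 shows otherwise.

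What the objection does not remove is that the stratifier is recorded for every patient before randomisation, and that leaving it out has no offsetting benefit.

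**Conclusion.** The point holds as a conditional recommendation on efficiency. The stated model omits the one variable on which randomisation was restricted. If that variable is prognostic beyond baseline, the between-subjects treatment test and the week-specific ANCOVAs are conservative and less precise than the design allows.

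The likely size is small. An R² of 0.20 would cost about 5 points (88.0 − 82.7 = 5.3), but a stratum effect that large has no support in the protocol. The direction is certain. The magnitude rests on assumed values of R², on the back-solved SD of 16.7, and on two-sided testing with 54 evaluable patients per arm.

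**What to change.** In the Statistical analysis section, name athletic/non-athletic status as a second between-subjects factor, as a main effect, in the repeated measures ANCOVA and in the follow-up univariate ANCOVAs. Physical activity is logged only during the first week, so include the stratum there as a factor in the single-period comparison between groups.

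The cost is one between-subjects residual degree of freedom (with 108 evaluable patients, 104 instead of 105). If the software adds stratum-by-time terms by default, these use further within-subject degrees of freedom, and the text should say whether they are kept. No new data are needed. Fixing this before the data are seen also avoids a later choice between adjusted and unadjusted results.

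### EM-filled values analysed as if observed would distort the repeated-measures ANCOVA, modestly at the planned 10% attrition and more beyond it; a likelihood-based mixed model avoids this at the same sample size

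*Protocol article*

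**What the plan says.** All of this is in the Statistical analysis section of the protocol article, apart from the attrition figure.

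- **Population:** "Analysis will be on an intention to treat basis".
- **Model, for every outcome:** "a within subject repeated measures analysis of covariance (ANCOVA) will be calculated to determine significant changes over time between groups". The layout is "Time (four levels: week 1, 2, 3 & 4) will be the within subject factor, with baseline values (week 0) used as the covariate".
- **Sphericity:** if Mauchly's test fails, "the Greenhouse-Geisser epsilon procedure will be carried out to adjust the degrees of freedom accordingly". This step marks the model as the classical repeated-measures procedure and not a mixed model.
- **Follow-up tests:** if group and time interact, a univariate ANCOVA is run to locate the week.
- **Missing values:** "If required, analyses will be undertaken using the expectation maximisation algorithm method to impute missing values". Nothing else is said on the matter. There is no multiple imputation and no variance correction. The section does not say what makes imputation required, or which variables enter the EM step.
- **Expected loss (Sample size section):** 60 patients per group, "allowing for a 10% attrition rate".

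**The concern.** The classical procedure takes only patients with all four weekly values. One missed visit removes the patient unless the gap is filled, so the plan has two routes.

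- **No EM:** incomplete patients drop out, which does not fit an intention-to-treat analysis.
- **EM:** a filled value is a conditional expectation. It has no residual scatter, yet it counts as a full observation. If arm is in the EM step, the estimate is sound but its standard error is too small. If arm is left out, filled values are drawn towards the pooled mean and the treatment difference shrinks.

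At stake are the confidence intervals, the 5% error rate and, in the second variant, the size of the estimated effect. The primary outcome is affected, because the same method serves all outcomes.

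**Working it through.** **1. The plan's own figure.** For two means, n per group = 2(z₀.₉₇₅ + z₀.₈₀)² SD² / Δ², with Δ = 9 points from the Sample size section and (1.960 + 0.842)² = 7.849. The document does not give the SD. Working back from 60 × 0.9 = 54 per group, the SD lies between √(53 × 81 / 15.698) = 16.54 and √(54 × 81 / 15.698) = 16.69, assuming a two-sided test. So 60 per group is attainable but cannot be verified. What matters here is that the plan foresees losing 12 of 120.

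**2. Complete cases if EM is not used.**
- 10% attrition in total: 120 × 0.9 = 108 remain, so 12 are lost.
- Scenario, 5% of visits missed independently: 120 × 0.95⁴ ≈ 98 remain.
- Scenario, 10% of visits missed independently: 120 × 0.9⁴ ≈ 79 remain.

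**3. Week-4 standard error by hand, arm in the EM step.** Let m be the fraction missing at week 4. Let R² be the share of week-4 variance that weeks 1-3 explain after adjustment for arm and baseline. Let n be the total sample.
- Filled values have variance R²σ² instead of σ², so the ANCOVA reports a variance of (4σ²/n) × [1 − m(1 − R²)].
- The true variance is (4σ²/n) × (1 − mR²)/(1 − m).
- Reported SE / true SE = √{[1 − m(1 − R²)](1 − m)/(1 − mR²)}.

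Assume a common correlation ρ among all five measurements. After baseline adjustment the weeks correlate r = ρ/(1 + ρ), and R² = 3r²/(1 + 2r).
- ρ = 0.5: r = 0.333, R² = 0.20. At m = 0.1 the ratio is √(0.92 × 0.90/0.98) = 0.92. At m = 0.2 it is √(0.84 × 0.80/0.96) = 0.84.
- ρ = 0.7: r = 0.412, R² = 0.28. The ratios are 0.93 and 0.85.

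Type I error is about P(|Z| > 1.96 × ratio): 7.2% and 10.1% for ρ = 0.5, and 6.9% and 9.5% for ρ = 0.7.

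**4. Simulation.** Assumptions: 60 per arm, SD 16.5, ρ = 0.5, dropout completely at random without return, 600 trials per row. The Monte Carlo error of a 5% rejection rate is about 0.9 points. Entries are reported SE / true SE, with type I error in brackets.

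| Dropout | EM with arm, week 4 | EM with arm, mean of weeks 1-4 | Mixed model, week 4 | Mixed model, mean of weeks 1-4 |
|---|---|---|---|---|
| 10% | 0.93 (8.0%) | 0.95 (5.7%) | 1.02 (4.2%) | 1.00 (5.0%) |
| 20% | 0.83 (9.5%) | 0.89 (7.7%) | 1.02 (3.8%) | 0.99 (5.5%) |
| 30% | 0.74 (15.3%) | 0.84 (9.7%) | 1.03 (3.3%) | 0.99 (5.7%) |

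The EM columns agree with the hand formula. The mixed model here had a random intercept, with week-by-arm and week-by-baseline terms.

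Larger runs (2,000 or more trials per setting, ρ of 0.5 or 0.7, intermittent or monotone gaps) put the week-4 SE at 10% missing about 7-11% too small, with type I error of 7.0-8.3%. At 20% missing they gave 16-19% and 10.4-11.4%. The ranges in the verdict cover all the runs, apart from one noisy setting discussed under the objection.

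**5. Arm left out of the EM step.** The SE ratio is about 1.0 and type I error about 5%, but a true difference of 9 points is understated.
- 10% dropout: by 0.39 (mean of weeks 1-4) and 0.49 points (week 4). 0.39/9 = 4% and 0.49/9 = 5%.
- 30% dropout: by 1.32 and 1.76 points, which is 15% and 20%.

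**The case against.** **The labels are inferred.** The article says neither that imputation is single nor that incomplete patients are dropped. The source cited for EM is not at hand, and a fuller document might specify added noise, several imputations or the variables used. This stands as a caveat. It does not remove the point: the article names the model and the filling method, and names no step that would correct the variance.

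**The two routes exclude each other.** In any one analysis either patients are dropped or gaps are filled. Likewise, standard errors that are too small and an effect that shrinks belong to different ways of running EM. This is correct. A reader might infer that the plan suffers all these faults at once; the text supports only that each available route has one.

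**A third of patients lost?** A reader might infer this from 1 − 0.9⁴ = 34%. That figure needs every patient to miss each visit independently with probability 10%. The protocol plans for 10% attrition, which gives about 12 patients, and the sample size already allows for that loss.

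**Larger distortion at 10% missing?** One 600-trial setting gave an SE 14% too small and 10.3% type I error. That rejection rate exceeded those at 20% missing in the same set (9.7% and 9.5%), and larger runs did not reproduce it. It should be read as simulation noise.

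**Week 4 is a follow-up contrast.** Univariate ANCOVAs are run only after a significant interaction. For the mean over weeks the distortion is smaller, which is why both are shown. The group-by-week test itself was not simulated.

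**Multiple imputation alone would do.** Properly combined multiple imputation by arm would also cure the fault, so replacing the model is the simpler of two valid remedies and not the only one.

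**Conclusion.** The point holds at moderate strength. The plan fixes a model that cannot use incomplete patients, and fills gaps by a method that, read naturally, treats estimates as data.

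- **10% missing, arm in the EM step:** week-4 SEs about 6-11% too small, type I error about 6-8%. Mean of weeks 1-4: about 2-6% too small, type I error about 5-7%.
- **10% missing, arm left out:** effect shrunk by about 4-5%.
- **20% missing, arm in the EM step:** week-4 SEs about 14-19% too small, type I error about 9-11%.
- **EM not used:** about 12 of 120 patients leave the analysis at 10% total attrition, and more if visits are missed intermittently, contrary to the intention-to-treat statement.

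These figures assume correlations of 0.5-0.7, normal data and values missing completely at random; the document gives none of these inputs. A reader might also infer that a mixed model solves the missing-data problem outright. It does not: it is valid only if data are missing at random, and a patient with no follow-up visit adds nothing to it.

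**What to change.** - **Primary analysis:** replace the repeated-measures ANCOVA with a linear mixed model for weeks 1-4, fitted by restricted maximum likelihood to every observed follow-up value of all randomised patients. Terms: group, week, group-by-week, baseline and the athletic/non-athletic stratum used in randomisation, with unstructured within-patient covariance. The sphericity test and its correction are then not needed.
- **Missing values:** state that EM-filled values will not be analysed as observed data. If imputation is wanted, use multiple imputation by arm with properly combined variances.
- **Sensitivity:** add one analysis that departs from missing at random.

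The change is to analysis wording only. The planned 120 patients, the visits and the data collected stay as they are. The cost is slightly more analyst time and open reliance on missing at random. The simulated model had a random intercept and no stratum, so the fuller model should be tried on simulated data before the wording is fixed.
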